Randomization will be conducted in blocks of 6 individuals, with permutation in the order and size of the blocks, generated by the website www.randomization.com (accessed on 1 September 2023) and managed by an assistant with no affiliation to the project. Allocation will be carried out using opaque, sealed, standardized envelopes, which will be numbered and assigned to each participant, opened after the individual has been included in the study. The assessing researchers and participants will remain unaware of the type of intervention administered until the study is completed. Protocol implementation will be the responsibility of a researcher who will not collect data and will not be involved in any other aspect of the study, except for protocol application, to ensure blinding.

Exclusion criteria include the following: individuals with comorbid diagnoses of depression or substance use disorder, as defined by the DSM-5, assessed by the SCID; patients who meet DSM-5 diagnostic criteria for organic brain mental disorder or intellectual disability; psychotic episodes or prominent positive symptoms (PANSS positive scale ≥ 20) during the protocol; clinically determined neurological disorders (e.g., epilepsy and a history of seizures or syncope, traumatic brain injury) or severe clinical conditions; the presence of metal implants, such as pacemakers, cochlear implants, implanted electrodes/stimulators, aneurysm clips/coils, stents, or any other criteria common to TMS protocols; any condition that prevents the participant from attending the 5 treatment days.

The study will be conducted at the Integrated Mental Health Care Center Hospital (CAISM) in São Paulo, Brazil.

*Procedures*:

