Patients who agree to participate in the study will be included in the sample after signing the Informed Consent Form. The research will be conducted in three phases (Figure 1): Baseline (T0, week 1): During the initial assessment, screening will be performed to verify inclusion and exclusion criteria. Individuals meeting the study criteria will be randomized into the intervention or sham group and will undergo clinical evaluation, heart rate variability (HRV) assessment, and neuropsychological evaluation. Patients must demonstrate clinical stability over the past three months, maintaining a positive psychopathology that is at most moderate (less than or equal to 4 on the items for positive symptoms of the Positive and Negative Syndrome Scale (PANSS) and exhibiting moderate or more severe negative symptoms, defined by scores equal to or greater than 20 on the Brief Negative Symptom Assessment Scale (BNSS). In this phase, baseline HRV will be measured, randomization will be defined, and measurements of the skull cap will be conducted according to the International 10–20 System reference for electroencephalography. Thus, the F3 area (corresponding to the left DLPFC) will be identified using the Beam F3 measurement system [36]. Intensity will be defined by identifying the lowest visible motor response (hotspot), with single pulses on the motor cortex using the lowest power of the equipment, through an automatic measurement system. For this, electromyography, EMG Neuro emg micro-2, (Neurosoft, Ivanovo, Russia)^®^, will be used, with electrodes positioned on the right abductor pollicis brevis muscle. During this phase, the individual will undergo a Safety Inventory for transcranial magnetic stimulation in adults. Intervention and reassessment (T1, week 2): The individual will undergo the protocol, consisting of 20 (twenty) intermittent theta burst stimulation (iTBS) sessions, conducted in 4 daily sessions over 5 consecutive days, i.e., one iTBS session per hour. This protocol corresponds to the total number of sessions conducted by Bation and colleagues; however, it was executed in half the time [16]. The protocol will be conducted with the patient seated in a chair. The coil will be positioned tangentially and perpendicular to the scalp in the area previously marked on a cap. At the end of each treatment day, an Adverse Effects Scale will be used to assess the safety of the technique. Upon completion of the protocol, initial clinical evaluations will be reapplied in the following week, as well as the heart rate variability (HRV) assessment and neuropsychological evaluation. T2 (week 3)—Follow-up 30 days: All assessments will be reapplied 30 days after the intervention.

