### 2.5. Statistical Analysis

The effects of the intervention will be analyzed according to the intention-to-treat (ITT) paradigm, which assesses the effect on all participants, regardless of their level of adherence to the treatment. The primary outcome of the study will be the reduction of negative symptoms, measured by the total score of the Brief Negative Symptom Scale (BNSS) with a score ≥20, while the secondary outcomes will focus on the reduction of negative symptoms as assessed by the negative symptom subscale score of the Positive and Negative Syndrome Scale (PANSS), the sub-domains of BNSS and physiological variables, through HRV assessment, sleep alterations and their association with negative symptoms, assessed by Pittsburgh and Epworth scales, and cognitive assessment by the MATRICS.

Missing data during follow-up will be handled using the restricted maximum likelihood method in mixed-effects linear regression analyses, allowing for the use of all data regardless of whether a participant completes the study, consistent with ITT analysis.

Clinical and demographic differences between groups will be initially evaluated at baseline using the Chi-square test for categorical variables and Student’s *t*-test for independent samples in continuous variables. These same tests will also be employed to identify potential differences between participants who complete the study and those considered to be dropouts. A participant will be considered a dropout if they miss any of the intervention protocol sessions, resulting in a loss of four sessions of intermittent theta burst stimulation (iTBS). A significance level of *p* < 0.05 will be adopted in all statistical analyses.

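### Randomisation is placed at T0 in week 1 although stimulation starts in week 2, so people lost in the gap enter the ITT set unexposed: a modest, avoidable loss of power

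*Protocol article*

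**What the plan says.** All of this comes from the protocol article.

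- **Time of allocation.** In section 2, Materials and Methods (Procedures), the baseline phase is T0, week 1. There, "Individuals meeting the study criteria will be randomized into the intervention or sham group", followed by clinical, HRV and neuropsychological assessment. The same paragraph repeats the placement: "In this phase, baseline HRV will be measured, randomization will be defined". Eligibility is screened before this step.
- **Other T0 steps.** Cap marking and motor-threshold measurement are also in this phase. So is a safety check: "During this phase, the individual will undergo a Safety Inventory for transcranial magnetic stimulation in adults". The text does not say whether these come before or after allocation.
- **Start of treatment.** Stimulation belongs to the next phase: "Intervention and reassessment (T1, week 2): The individual will undergo the protocol".
- **Envelope.** Section 2 (randomisation paragraph) says that it is "opened after the individual has been included in the study". Under Procedures, patients "will be included in the sample after signing the Informed Consent Form". Nothing ties the opening to the first session.
- **Analysis set.** Section 2.5 applies intention to treat, "which assesses the effect on all participants, regardless of their level of adherence to the treatment", with missing follow-up data handled by restricted maximum likelihood in a mixed model.
- **Sample size.** Section 2 (Participants) sets 30 per group, f = 0.38, two-tailed 5% and a stated power of 0.82. It mentions no allowance for loss.

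**The concern.** Ratings, HRV, cognition, cap marking, motor threshold and the safety inventory are the same in both arms. The only person who uses the allocation is the applicator, who has to fit the active or the sham coil (section 4, Limitations), and that need arises at session 1. Allocating in week 1 therefore gains nothing and opens an interval in which a randomised person can be lost before any exposure.

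Under the stated analysis such a person counts in one of two ways:

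- **No T1 BNSS.** The mixed model keeps the baseline record, but that adds almost nothing to the group-by-time contrast, so the comparison shrinks.
- **T1 BNSS obtained without stimulation.** In the active arm this person contributes no treatment effect, so the estimate moves towards zero.

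Both are avoidable. The same person lost before the envelope is opened would never have been randomised. The problem also does not depend on whether the T0 assessments come before or after allocation: it remains if the envelope is opened at the very end of the T0 visit.

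**Working it through.** **Inputs from the article (section 2, Participants):** 30 per arm, f = 0.38, two-sided alpha 0.05, stated power 0.82.

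**Assumption:** a share L of each arm is lost between T0 and session 1. The article gives no rate, so L = 3%, 5% and 10% are shown.

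**1. Reproduce the plan's figure.** For two equal groups d = 2f = 2 × 0.38 = 0.76. The two-sample t test has 58 degrees of freedom and noncentrality d × √(n/2) = 0.76 × √15 = 2.94. Power is 0.825. The equivalent F test, with noncentrality f² × N = 0.1444 × 60 = 8.66 on 1 and 58 degrees of freedom, also gives 0.825. The stated 0.82 is reproduced. It assumes that all 60 contribute T1 data with the full effect.

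**2. Lost and unmeasured.** The size per arm becomes 30 × (1 − L), with d unchanged.

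**3. Measured but untreated.** The size stays at 30 per arm. Only the treated share of the active arm carries the effect, so d becomes 0.76 × (1 − L).

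| Assumed L | n per arm if unmeasured | Power | d if measured but untreated | Power |
|---|---|---|---|---|
| 0 | 30 | 0.825 | 0.760 | 0.825 |
| 3% | 29.1 | 0.813 | 0.737 | 0.802 |
| 5% | 28.5 | 0.805 | 0.722 | 0.785 |
| 10% | 27.0 | 0.782 | 0.684 | 0.741 |

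In people, 5% is 3 of 60 and 10% is 6 of 60.

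**4. Margin over 80% in whole participants.** With no T1 data from those lost, 29 against 29 gives 0.812 and 28 against 28 gives 0.798. The plan can lose about one person per arm before it falls below 0.80.

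**The case against.** Randomising at baseline, treating in the next scheduled week and analysing by intention to treat is a coherent design, and no statement in the article contradicts another here. Several limits on the point stand.

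- **Main eligibility is settled first.** A reader might infer that unsuitable people are routinely allocated. The text does not support that: only those who meet the criteria are randomised, and inability to attend the treatment days is itself an exclusion criterion. What remains is new events and withdrawals, plus the safety inventory and motor threshold, whose order is not stated. The exclusion for psychotic episodes or prominent positive symptoms arising during the protocol could also apply after session 1, and later allocation would not prevent that.
- **The gap may be short.** The article gives week numbers only, so the interval could be a few days.
- **No bias between arms follows.** A reader might infer a distorted comparison. Participants and assessors are blinded, so loss before session 1 should not depend on arm.
- **The size is assumed.** At 3% loss power stays above 0.80 in both scenarios. The lowest figures require people who never started to return for T1 rating, which is the less likely case.
- **Part of the remedy is recruitment.** Moving the envelope does not by itself restore numbers. Recruiting more under the present schedule would also offset unmeasured losses: 60/0.95 = 63.2, so 64, and 60/0.90 = 66.7, so 67.

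One might add that an article condenses the full protocol, so the day on which the envelope is opened could be specified elsewhere. That does not remove the point, because the article itself twice places randomisation in week 1. Nor does extra recruitment keep unexposed people out of the intention-to-treat set. Only later allocation does that.

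**Conclusion.** The point holds as a minor one. The article states an allocation time that is earlier than any procedure needs, and its intention-to-treat rule then retains people who never reached session 1. The consequence is reduced power or an attenuated estimate, similar in both arms.

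Under assumed losses of 3% to 10%, power falls from 0.825 to between 0.813 and 0.782 if those people are unmeasured, or to between 0.802 and 0.741 if they are measured but untreated. These figures rest on the plan's own effect size, on a two-group comparison that reproduces its power, and on loss rates that the article does not supply. They do not show that the trial is underpowered. They show that its margin over 80% is about one participant per arm, so avoidable losses are worth avoiding.

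**What to change.** In section 2, amend the randomisation paragraph and Procedures to state that:

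1. all T0 assessments and suitability checks, including the safety inventory and motor threshold, are completed before allocation;
2. the unblinded applicator opens the envelope on the first treatment day, immediately before session 1, after a brief check that the participant is still eligible;
3. people lost before that moment are not randomised, and intention to treat applies from that moment on.

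**Cost.** The text change is a few sentences, plus a short eligibility check on the day. The applicator learns which coil to fit only that day. If 30 randomised per arm is to be kept, each person lost before randomisation has to be replaced, which means extra recruitment and a repeated T0 work-up (diagnostic interview, ratings, cognitive battery, HRV and motor threshold). The change in envelope timing is worth making even without replacement, because it keeps people who never started out of the analysis set.

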### 2.1. iTBS Protocol

The treatment will be conducted using a figure-eight coil positioned over the left DLPFC at a 45-degree angle to the midline, utilizing the Neuro—MS/D device (Neurosoft, Ivanovo, Russia)^®^, controlled by Neuro-MS.NET software (version 3.2.11.0 released 16 July 2023 18:13 x64, Debug), coupled with a rapid recharge module. The intensity will be set at 100% of the observed resting motor threshold, adhering to ethical and safety criteria [37]. The parameters will consist of three pulses at a frequency of 50 Hz, at 5 Hz, using a 2 s train, with an inter-train interval of 8 s, totaling 190 s. Four daily sessions will be conducted hourly, delivering 600 pulses per session. The sham stimulation will replicate the same parameters with coil positioning tangentially to the scalp but will use a sham coil (placebo) to avoid measurable biological effects. The sham coil has an identical appearance to its active version, mimicking its operation; however, it does not produce electromagnetic pulses, thus not promoting a clinical effect. In this way, the subjective somatic sensation on the scalp and the acoustic artifacts during stimulation will be the same for both active and sham volunteers [20,38].

### 2.2. Clinical Assessment

Clinical assessment will be applied three times: at baseline (T0), after the iTBS (T1), and at a 30-day follow-up (T2). The validated Portuguese versions for the Brazilian population of the Brief Negative Symptom Scale (BNSS) [39], and the Positive and Negative Syndrome Scale (PANSS) [40] will be applied to assess negative symptoms and clinical symptomatology. Additionally, the translated and validated versions of the Pittsburgh Sleep Quality Index (PSQI) [41] and the Epworth Sleepiness Scale (ESE) [42] will be used to assess sleep. Generalized Anxiety Disorder-7 (GAD-7) [43] and Clinical Global Impression (CGI) [44], validated instruments for evaluating symptom severity in patients with schizophrenia in Brazil, will also be employed. The Calgary Depression Severity Scale (CDSS) [45] will be applied to check for depressive symptoms. Finally, the Simpson–Angus Scale (SAS) [46] will be administered to identify medication-induced parkinsonian symptoms. All tests will be conducted by trained psychiatrists.

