A recent meta-analysis that included 12 intervention studies using intermittent theta burst stimulation (iTBS) for negative symptoms showed that a higher total number of pulses, compared to relatively lower numbers of pulses, presents a greater effect size, suggesting that the efficacy of iTBS treatment is dose-dependent [11]. Definitions of parameters such as intensity, frequency, duration, waveform, and stimulation site need to be better defined. In this regard, accelerated TMS (aTMS) protocols, characterized by two or more sessions of TMS in a single day, have emerged as an effective alternative and appear to be a viable strategy for reducing total treatment time; it enables a greater number of sessions per day and delivers the same number of pulses and sessions of a conventional 6-week treatment within a single week, sometimes with efficacy surpassing that of daily session doses [12,13,14]. Despite its potential, the literature about the use of intermittent theta burst stimulation (iTBS) for treating negative symptoms of schizophrenia is still limited, especially regarding the type of protocol and the brain area to be stimulated, although the left dorsolateral prefrontal cortex (DLPFC) has shown promising results [15,16,17,18,19].

The studies conducted to date have limitations that hinder a better understanding of the true potential of intermittent theta burst stimulation (iTBS) for negative symptoms in schizophrenia, including the following: 1—few double-blind, randomized clinical trials; 2—small sample sizes; 3—the use of instruments that do not allow for the assessment of sub-domains of negative symptoms; 4—a lack of control for potential confounders in the evaluation of negative symptoms, such as depressive and extrapyramidal symptoms [15,16,17,20,21].

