## 2. Materials and Methods

Design: We proposed a randomized, double-blind, sham-controlled clinical trial to test the effects of the accelerated iTBS protocol in participants with schizophrenia with negative symptoms (CONSORT—Figure 1). The study is conducted in accordance with the Declaration of Helsinki and has been approved by the Research Ethics Committee of the Federal University of São Paulo (UNIFESP) as of 14 September 2023 and registered in The Brazilian Registry of Clinical Trials (ReBEC) (CAEE: 71102823.4.0000.5505).

*Participants*:

We will recruit 60 volunteers, aged between 18 and 50 years of both genders, who have been diagnosed with schizophrenia according to the criteria of the Diagnostic and Statistical Manual of Mental Disorders (DSM-5), through an evaluation conducted via the Structured Clinical Interview for DSM-5 (SCID-5) and who present negative symptoms of moderate intensity (score ≥ 20 on the BNSS). Participants must have stable medication use, with no changes in antipsychotics in the three months prior to inclusion, and must not be using medications that could lower the seizure threshold, except for antipsychotics. Additionally, participants should not have a history of substance dependence or alcohol use in the past four weeks. In the case of smokers, the number of cigarettes and the last use will be documented. Regarding neuromodulation, participants should not have undergone any brain stimulation protocols in the past year prior to study enrollment. All participants must sign the informed consent form to participate in the study.

Participants will be allocated into two groups (intervention and sham), with 30 subjects per group. The statistical power for the primary analysis with this sample size is estimated to be β = 0.82. This calculation assumes (1) the use of mixed linear regression models for hypothesis testing, which will assess the interaction between time (baseline vs. T1) and treatment (intervention vs. sham), (2) a moderate effect size (f = 0.38), and (3) a significance level of 5% (two-tailed).

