Differences between the baseline, after intervention, and follow-up (T0, T1, and T2) for each measure will be tested using mixed-effects linear models. The treatment effect will be estimated through the interaction between the intervention group (intervention or sham) and the assessment time (T0, T1, and T2). Effect estimates will be presented as post-intervention mean differences, along with 95% confidence intervals, *p*-values, and Cohen’s d effect sizes (where 0.2 represents a small effect, 0.5 represents a moderate effect, and 0.8 represents a large effect). Random effects from repeated measures within each subject will be modeled according to the covariance structure that shows the lowest index based on the Akaike information criterion (AIC). The following covariates will be included in the models: the Calgary Depression Severity Scale score, as depressive symptoms may confound the assessment of negative symptoms and individuals with severe depression will be excluded from the sample; the total score of the Clinical Global Impression-Severity scale (CGI-S), since the severity of illness may influence treatment response; and the Generalized Anxiety Disorder 7-item scale (GAD-7), due to anxiety symptoms. For the various exploratory analyses conducted with the previously detailed secondary outcomes, the significance value will be corrected for multiple tests using Bonferroni criterion, with an alpha of 0.05 divided by the number of tests.

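### The Simpson–Angus score is collected at every visit and extrapyramidal symptoms are named as a confounder, but the fixed covariate list omits the score (low-severity improvement)

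*Protocol article*

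**What the plan says.** - **Introduction.** The fourth limitation listed for earlier iTBS studies is "a lack of control for potential confounders in the evaluation of negative symptoms, such as depressive and extrapyramidal symptoms". The two confounders are named together.
- **Section 2.2, Clinical Assessment.** The battery is given at baseline (T0), after stimulation (T1) and at the 30-day follow-up (T2). Within it, "the Simpson–Angus Scale (SAS) [46] will be administered to identify medication-induced parkinsonian symptoms".
- **Section 2.5, Statistical Analysis.** The covariate list opens with "The following covariates will be included in the models: the Calgary Depression Severity Scale score, as depressive symptoms may confound the assessment of negative symptoms", continues with "the total score of the Clinical Global Impression-Severity scale (CGI-S), since the severity of illness may influence treatment response" and ends with "and the Generalized Anxiety Disorder 7-item scale (GAD-7), due to anxiety symptoms". Each member has its own reason, and the list reads as closed.
- **Elsewhere.** The SAS is not named among the outcomes, the covariates or the eligibility criteria. Its only other mentions are in the Figure 1 legend and the abbreviation list. The nearest related rule is the entry requirement of stable medication, "with no changes in antipsychotics in the three months prior to inclusion".
- **Primary contrast.** Both the sample size paragraph of Section 2 and Section 2.5 estimate the treatment effect through the interaction of group and assessment time.

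**The concern.** The article gives confounding of negative-symptom ratings as its reason for adjusting for depression. It applies the same reasoning to extrapyramidal symptoms in the Introduction, plans to measure them, and then leaves them out of the model. GAD-7, a measure of anxiety, which the Introduction does not name as a confounder, is in.

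Parkinsonism can look like blunted affect or reduced movement on a negative-symptom scale. The randomisation described is blocked, with no stratification by SAS, so arms of 30 can differ by chance at baseline. If baseline SAS also predicts how BNSS changes, that difference carries into the estimate uncorrected. If investigators notice an imbalance later and add SAS then, the adjustment becomes a post hoc choice on the primary outcome. Settling it in advance avoids this.

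**Working it through.** **Inputs from the article:** 30 per group, N = 60; f = 0.38; two-sided alpha 0.05; stated power 0.82 (Section 2). For two equal groups d = 2f = 0.76. **Assumed:** the partial correlation r between baseline SAS and BNSS change, taken as 0 to 0.4, because the documents give none.

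**1. The plan's own figure.** The noncentrality is f²N = 0.38² × 60 = 8.664. An F test on 1 and 58 degrees of freedom gives power 0.825, which agrees with 0.82.

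**2. Chance imbalance.** The SE of the between-arm difference in a standardised baseline score is √(2/30) = 0.258.
- P(|difference| > 0.3 SD): 0.3/0.258 = 1.16, so about 0.25.
- P(|difference| > 0.5 SD): 0.5/0.258 = 1.94, so about 0.05.

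These probabilities hold for any baseline variable. An imbalance moves the result only in proportion to r. At the 95% limit, 1.96 × 0.258 = 0.506 SD, the shift in the standardised group difference in change is r × 0.506:
- r = 0: 0
- r = 0.1: 0.05
- r = 0.2: 0.10
- r = 0.4: 0.20

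The planned d is 0.76. A typical imbalance is smaller: the mean absolute difference is 0.258 × √(2/π) = 0.206 SD, which shifts the result by 0.08 at r = 0.4.

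**3. Precision.** Adjustment removes a fraction r² of the residual variance, so the noncentrality becomes 8.664/(1 − r²). In complete data, with each covariate interacting with visit, the T0-to-T1 contrast amounts to a regression of change on group and covariates. With four covariates this leaves 60 − 2 − 4 = 54 degrees of freedom.

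| r | Variance removed | Power |
|---|---|---|
| 0 | 0% | 0.824 |
| 0.1 | 1% | 0.828 |
| 0.2 | 4% | 0.839 |
| 0.3 | 9% | 0.858 |
| 0.4 | 16% | 0.884 |

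A simulation of the adjusted analysis gave slightly less: 0.836, 0.853 and 0.873 at r = 0.2, 0.3 and 0.4. This is why the upper end is given as 0.87–0.88.

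**4. Cost if SAS is unrelated to outcome.** Going from three such covariates to four moves the degrees of freedom from 55 to 54 and power from 0.8243 to 0.8240, a loss of 0.0003.

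**5. Form of the covariate.** A baseline score that enters only as a main effect shifts all of a patient's visits equally. It therefore leaves the group-by-time estimate unchanged in complete data. A check on one simulated three-visit data set gave the same T1 interaction estimate with no SAS term and with a SAS main effect (−3.82 both times); it moved (to −3.33) only when SAS-by-visit was added. With three visits, SAS and its visit interaction use 1 + 2 = 3 parameters.

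**The case against.** The strongest reply is that randomisation already deals with confounding of the treatment comparison. A reader might infer from the Introduction that omitting SAS biases this trial, or that the trial simply repeats the flaw it criticises. The documents do not support either reading. Allocation is random, so omitting a baseline covariate does not bias the effect on average. The Introduction criticises earlier studies, among which it counts few double-blind randomised trials, and it does not promise adjustment for SAS.

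Second, mimicry of negative symptoms affects the level of BNSS. A steady contribution is present at both T0 and T1 and drops out of the group-by-time contrast. The rule of stable antipsychotics before entry makes steady scores more likely, although it does not cover changes after inclusion. This stands, and it means that imbalance matters only if baseline SAS predicts change.

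Third, one might say that the depressive half is handled and only the extrapyramidal half is not. That is too generous to the current list. Section 2.5 does not say whether the CDSS is a baseline or a time-varying value, and it gives no covariate-by-visit terms. A baseline CDSS main effect would also leave the contrast unchanged in complete data.

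Fourth, the correlation is assumed, has no floor in the documents, and may overlap with what CDSS, CGI-S and GAD-7 already explain. This also stands, so zero gain belongs in the range.

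Finally, the baseline comparison in Section 2.5 could include SAS and so display an imbalance. Displaying an imbalance does not adjust for it.

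**Conclusion.** The inconsistency is in the text: two confounders are named together, both are measured, and a closed list adjusts for only one of them, without a reason. It is not a detail left to an unseen analysis plan, because the article itself fixes the list and justifies each entry.

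The consequence is small. There is no bias on average. The loss is protection against a chance imbalance and, possibly, some precision: from nothing at r = 0 to a power gain of about 0.05 to 0.06 at r = 0.4. These figures rest on the stated f = 0.38, 30 per arm with complete data, and an assumed r that the documents neither give nor bound. This is a low-severity improvement, worth making because it costs almost nothing before unblinding and cannot be made cleanly afterwards.

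**What to change.** In Section 2.5:
- Add the T0 SAS score and its interaction with visit to the prespecified covariates of the BNSS model.
- State that CDSS, CGI-S and GAD-7 enter in the same form, as the T0 value with a visit interaction, so that all four can act on the group-by-time contrast.
- Keep T1 and T2 SAS values out of the primary model, since adjusting for post-randomisation scores could bias the treatment effect. They can be reported descriptively or in a sensitivity analysis.
- If the authors prefer to leave SAS out, give the reason, given what the Introduction says.

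The cost is a few sentences and no new data. SAS adds three parameters. Giving the three listed covariates a visit interaction adds 2 × 3 = 6 more if they would otherwise be main effects. For the T0-to-T1 contrast, the whole change takes the degrees of freedom from 58 to 54 and power from 0.8250 to 0.8240 if none of the four predicts change.
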